### 2.5. Circulating Biomarker Assessment

Venous blood samples were collected after enrollment and placed at -80 °C for long-term storage. 

Besides routine parameters (complete blood count (CBC), prothrombin time (PT), activated partial thromboplastin time (APTT), D-dimer, fibrinogen, low-density lipoprotein (LDL), high-density lipoprotein (HDL), triglycerides, glucose, creatinine, glomerular filtration rate (GFR), alanine aminotransferase, C-reactive protein (CRP), N Terminal pro B-type natriuretic peptide, Lp(a), troponin), several circulating biomarkers will be evaluated: Endothelial function biomarkers;Pro- and anti-inflammatory molecules;Metalloproteinases and their inhibitors;Markers of renal function;Markers of blood clotting activation and of fibrinolytic system of coagulation activation, including prothrombin fragment 1+2, thrombin–antithrombin complex, D-dimer, and endogenous thrombin potentials;Genetic polymorphisms that may influence the effect of anticoagulants and plasmatic microRNA profile.

The list of biomarkers under investigation is detailed in Table 1. The biological material (serum, plasma, DNA) is properly conserved to allow the evaluation of further biomarkers by specific or global assessment strategies (e.g., metabolomics profiling, targeted or whole-exome sequencing).

Proteomic and genetic biomarkers will be evaluated with high-multiplex immunoassays or high-throughput technologies such as Bio-Plex Multiplex Immunoassay System (BioRad), Proximity Extension Assay (Olink) technology, H-nuclear magnetic resonance spectroscopy (Bruker BioSpin), real-time PCR (Life Technologies), droplet digital PCR (BioRad), and high-throughput sequencing (Illumina).

Biosamples were processed using standard and harmonized operating procedures.

Clinical data are registered electronically in the web-based registry (http://www.strat-af.it/). Quality controls are done on a weekly basis. Imaging data are instantly checked for protocol conformity. 

The same clinical/functional assessment and brain MRI will be repeated 18 months after enrollment. An interim telephone follow-up interview will be scheduled approximately three months before the final clinical assessment. 

### 2.6. Primary Endpoint

The primary study endpoint will be SVD progression, evaluated by means of the control MRI performed 18 months after enrollment. The progression of lacunar infarcts and microbleeds will be evaluated as the appearance of at least one new lesion, respectively. White matter hyperintensities progression will be rated by means of the visual Rotterdam Progression Scale (score range from 0 to 9) [26]. Absence or presence of progression (0 or 1, respectively) will be rated in three periventricular regions (frontal caps, occipital caps, bands), four subcortical white matter regions (frontal, parietal, occipital, temporal), basal ganglia, and the infratentorial region. Post-processing and ratings will be centralized and performed by expert and reliable observers, blinded to clinical data.

### 2.7. Secondary Endpoints 

Secondary endpoints will be:Stroke occurrence (ischemic or hemorrhagic).Considering data from medical history and available laboratory and imaging exams, new major cerebrovascular events will be recorded as ischemic or hemorrhagic strokes. Ischemic strokes will be further categorized in subtypes according to the TOAST classification system [27]. Hemorrhagic strokes will be classified according to lesion type and location.Progression of global functioning, cognitive, and motor performances.Progression in cognitive status will be determined by the occurrence of a diagnosis of MCI or dementia, and defined according to performances on the comprehensive neuropsychological test battery (evaluated as normal or abnormal by means of national normative data), and functional status.The change in global functional status will be based on the Activities of Daily Living and Instrumental Activities of Daily Living scales, and the worsened condition will be defined as the loss of at least one item (i.e., the patient became dependent for an item function that was preserved at baseline evaluation).Motor status will be evaluated by means of the Short Physical Performance Battery. Based on the total score (range 0–12), at each visit individuals will be categorized as having normal (SPPB ≥ 11) or impaired mobility (SPPB ≤ 10), and variations in performance categories over time (baseline vs. 18 months) will be evaluated for each patient.

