## 3. Results

Starting from September 2017 until March 2019, 617 patients referring to the outpatient clinic of the Center of Thrombosis for oral anticoagulants therapy control were screened for inclusion in the study. As shown in Figure 1, 423 patients (68%) were excluded because of MRI contraindications (*n* = 227) or refusal (*n* = 196). The remaining 194 patients were enrolled. Demographic and clinical characteristics of the baseline sample are shown in Table 2: mean age was 78.1 ± 6.7 (range 65–97) years, 118 (61%) were males, and mean education was 9.1 ± 4.3 (range 2–19) years. The type of AF was paroxysmal in 93 patients (48%), and persistent or permanent in the remaining patients. Concerning the type of oral anticoagulant, 57 patients (29%) were on vitamin K antagonists, and 137 (71%) were on direct oral anticoagulants. Follow-up clinical evaluation and brain MR are ongoing.

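### Motor progression is measured only as a change between two SPPB categories, so a patient scoring 10 or below at baseline cannot register worsening

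*Protocol article*

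**What the plan says.** Section 2.7 of the protocol article includes "Progression of global functioning, cognitive, and motor performances" among the secondary endpoints. For the motor part it names the instrument ("Motor status will be evaluated by means of the Short Physical Performance Battery"), gives the total score a range of 0 to 12, and then reduces that score to two classes on both occasions: "individuals will be categorized as having normal (SPPB ≥ 11) or impaired mobility (SPPB ≤ 10), and variations in performance categories over time" are what will be compared. The comparison is individual and runs from baseline to the end of follow-up: "variations in performance categories over time (baseline vs. 18 months) will be evaluated for each patient".

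The section gives no change in the total score, no minimum point loss and no grading within the impaired class. Section 2.8 does not mention motor status.

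The functional endpoint in the same section is built differently. For the Activities of Daily Living scales, "the worsened condition will be defined as the loss of at least one item", judged against what that patient could do at baseline.

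The entry criteria in Sections 2.1 and 2.2 set no limit on mobility. Section 3 reports 194 patients enrolled, and "mean age was 78.1 ± 6.7 (range 65–97) years".

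**The concern.** An endpoint meant to capture progression should be able to record decline in anyone who can still decline. The cut-point puts 11 of the 13 possible scores (0 to 10) into one class and leaves 2 (11 and 12) in the other. Someone who enters in the lower class has no worse class to move to, however far the score falls. Someone who enters at 11 is counted as worse after losing one point.

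Two things are at stake. Motor worsening can be seen only in patients who start with near-maximal scores, so a reported rate of progression describes that subgroup and not the cohort. Most of the information in the score is also lost, which matters for any later attempt to relate markers to motor decline. The functional endpoint avoids this problem because it measures loss against the patient's own baseline. The article gives no reason for treating motor status differently.

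**Working it through.** The plan contains no power, event or sample-size figure for the motor endpoint (Section 2.2 sets the sample size by feasibility), so there is no stated figure to reproduce. The check has three steps.

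**1. Which declines does the rule detect?** Inputs from Section 2.7: integer scores 0 to 12; normal is 11 or more; impaired is 10 or less.

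- Possible worsening pairs (follow-up below baseline): 13 × 12 / 2 = 78.
- Pairs crossing from normal to impaired: baseline 11 or 12, follow-up 0 to 10, so 2 × 11 = 22.
- Missed pairs starting at 10 or below: 11 × 10 / 2 = 55.
- Missed pair within the normal class: 12 to 11, so 1.
- Check: 22 + 55 + 1 = 78. Share registered: 22 / 78 = 28%.

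This counts possibilities and does not weight them by how often they occur. It shows the structure of the rule, not an expected detection rate. With the total score all 78 pairs count, and every patient with a baseline score of 1 or more can worsen.

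**2. How many patients can register worsening?** The number is 194 × (1 − p), where p is the share at 10 or below at baseline. The document does not give p, so a range is assumed.

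| Assumed p | Able to register worsening, of 194 |
|---|---|
| 25% | about 146 |
| 30% | 136 |
| 50% | 97 |
| 70% | 58 |
| 80% | 39 |

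These figures are before any loss to follow-up.

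**3. What might this cost in power?** This is an illustration, and every input is an assumption: 155 patients with both visits (155 / 194 = 80%), two equal marker groups, a 0.6-point difference between groups in mean change, SD of change 1.6, mean decline 0.7 points, two-sided 5% test. The category rule is tested as a comparison of proportions among patients at 11 or above at baseline. The score is tested by ANCOVA of the 18-month score on baseline.

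| Baseline mean (SD) | At 10 or below | Power, category | Power, adjusted score |
|---|---|---|---|
| 8 (2.8) | 81% | 13% | 60% |
| 9 (2.5) | 73% | 16% | 63% |
| 10 (2.0) | 60% | 20% | 61% |
| 11 (1.5) | 37% | 29% | 57% |

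Across the wider set of scenarios tried, with 25% to 81% at 10 or below, power was about 12–33% for the category rule and 56–64% for the score. With all 194 patients, a 0.8-point difference and baseline SD 2.5, baseline means of 8, 9 and 10 gave about 17%, 28% and 38% for the category rule and 91–92% for the score. The levels move with the assumptions, but the score did better in every scenario.

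**The case against.** The strongest reply is that the article is a condensed account. It speaks of variations in category, which covers improvement as well as decline, and it does not say that the total score will go unanalysed. Onset of impaired mobility is also a recognisable outcome, and it parallels the cognitive endpoint in the same section, which counts new diagnoses of MCI or dementia.

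Part of this stands. Patients at 10 or below are not wholly uninformative, since they can be recorded as stable or improved, and the category change is worth keeping. But the article does not leave the motor definition open. It states the cut-point, the classes and the comparison, and that comparison is the only motor measure given. Under it, worsening from 10 or below cannot be recorded.

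Some stronger readings are tempting but not supported:

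- A reader might infer from the mean age of 78.1 that most of the cohort starts at 10 or below. Baseline SPPB is not reported. This is an outpatient cohort from which 423 of 617 screened patients were excluded for MRI contraindications or refusal, so selection towards better mobility is plausible.
- A reader might conclude that the study misses a power target for motor decline. No such target exists. Section 2.8 names SVD and its progression as the outcome variables and describes no model relating markers to SPPB.
- A reader might say that the rule excludes the patients of greatest interest. Nothing in the article singles out the frailest patients as the target of this endpoint; the stated aim is prediction of cerebral bleeding.

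**Conclusion.** The point holds as a defect in how one secondary endpoint is defined. That a patient at 10 or below cannot register worsening, and that 22 of 78 worsening pairs count, follows from the stated rule alone and needs no outside figure.

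The size of the effect in this cohort is uncertain. The range of about 146 down to 39 patients able to show worsening rests on an assumed 25–80% at 10 or below. The power figures rest on assumed group sizes, effect and variability, and show the direction and rough scale of the loss rather than a forecast. Confidence is therefore high in the logic and moderate in the magnitude. The change is worth making.

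**What to change.** Make the 18-month SPPB total score, adjusted for baseline SPPB, the main analysis of motor progression, using a linear model or, given the bounded ordinal scale, a proportional-odds model. State which of the two is chosen. Keep the category change as a supplement, and report new impairment only among patients at 11 or above at baseline, with that number as the denominator. Report the baseline SPPB distribution, so that readers can see how many patients the category rule leaves unable to worsen.

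No new data are needed: Section 2.3 collects the battery at baseline, and Section 2.5 repeats the same clinical and functional assessment at 18 months. The cost is a documented, dated change to a published secondary endpoint, made before the follow-up motor data are examined (the article reports follow-up as ongoing), and a main measure that is less immediately interpretable than a switch from normal to impaired.

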### 2.8. Statistical Analyses

Multivariate regression analyses will be performed in order to identify independent predictors of SVD and its progression. Among the variables of interest, apart from the clinical ones and those assessed by means of conventional MRI, special attention will be paid to the relationship with advanced neuroimaging features and circulating biological markers.

Cerebral SVD and its progression—particularly microbleeds, which are considered the main expression of a bleeding-prone state—will be studied as outcome variables in multivariate regression models, considering the independent effect of all relevant markers, including major vascular risk factors and anticoagulant treatment with different types of anticoagulants (vitamin K antagonists vs. direct thrombin antagonists or factor Xa antagonists), and circulating biomarkers. 

Interactions of circulating biomarkers with imaging markers, and types of oral anticoagulants will also be analyzed. Bonferroni correction will be applied in multivariate models to counteract the problem of multiple comparisons.

The multivariable prediction of the risk of SVD progression in this cohort of AF patients on oral anticoagulants will be studied as the methodological background for clinical research in the setting of stroke prevention in patients with AF (i.e., for designing and sample sizing studies potentially adopting the above indicated biomarkers as surrogate markers of the clinical outcomes).

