## Figures and Tables

**Figure 1 medicina-55-00626-f001:**
[figure not shown]
Strat-AF flow diagram.

**Table 1 medicina-55-00626-t001:** Circulating biomarkers under investigation in the Strat-AF study.

Category	Biomarkers Name
Markers of endothelial function	- von Willebrand Factor (vWF) - Tissue Factor Pathway Inhibitor (TFPI)
Pro- and anti-inflammatory molecules	- Chemokine (C-C motif) ligand 3 (CCL3) - Interleukin (IL)-1β (IL-1β), - IL-1 Receptor antagonist (IL-1RA) - IL-2 - IL-6 - IL-8 - IL-10 - IL-12 P40 - Tumor Necrosis Factor Alpha (TNF-Alfa) - Intercellular Adhesion Molecule-1 (ICAM-1) - Vascular cell adhesion molecule-1 (VCAM-1) - Vascular Endothelial Factor (VEGF)
Metalloproteinases	- Matrix metalloproteinase (MMP)-2, MMP-8, MMP-9, MMP-12 - Tissue Inhibitor of Metalloproteinases (TIMP)-1, TIMP-2, TIMP-3, TIMP-4
Markers of coagulation activation	- Endogenous thrombin potential (ETP) - Plasminogen activator inhibitor-1 (PAI-1) antigen - Prothrombin fragment 1+2 (F1+2) - Thrombin antithrombin complexes (TAT) - Tissue factor - Plasminogen Activator Inhibitor-1 (PAI-1) antigen - Clot lysis time (CLT)
Genetic polymorphisms and plasmatic miRNA	- CES1 rs2244613 - CES1 rs8192935 - ABCB1 rs148738 - VKORC1 G3673A or –1639G>A rs9923231 - CYP2C9*2 rs1799853 - CYP2C9*3 rs1057910 - CYP2C9*5 rs28371686 - CYP2C9*6 rs9332131 - CYP4F2 V433M rs2108622 C>T - GGCX rs11676382 - Plasmatic miRNA profiling by real-time PCR

**Table 2 medicina-55-00626-t002:** Baseline sample demographic and clinical characteristics.

	Min–Max	Baseline Sample *n* = 194
Age, years (mean ± SD)	65–97	78.1 ± 6.7
Years of education	2–19	9.1 ± 4.3
Sex (% males)	-	61% (*n* = 118)
Hypertension	-	82% (*n* = 159)
Hypercholesterolemia	-	48% (*n* = 94)
Diabetes	-	13% (*n* = 25)
Smoking habits	-	61% (*n* = 119)
History of stroke	-	22% (*n* = 42)
Alcohol consumption	-	51% (*n* = 100)
Paroxysmal AF	-	48% (*n* = 93)
Type of oral anticoagulant Vitamin K antagonists Direct oral anticoagulants	- -	29% (*n* = 57) 71% (*n* = 137)

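### Section 2.8 fixes plain Bonferroni; Holm over the same tests gives the same error control and never less power, and naming new microbleeds as lead outcome would settle error across outcomes

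*Protocol article*

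**What the plan says.** Section 2.8 plans regression models for SVD and its progression, and names one multiplicity method: "Bonferroni correction will be applied in multivariate models to counteract the problem of multiple comparisons". It gives no alpha, no number of tests and no statement of which tests form the family.

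The outcome variables are described as "Cerebral SVD and its progression—particularly microbleeds, which are considered the main expression of a bleeding-prone state". The models are to be built "considering the independent effect of all relevant markers", and the same section adds: "Interactions of circulating biomarkers with imaging markers, and types of oral anticoagulants will also be analyzed".

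Section 2.6 rates the primary endpoint in three separate parts. For two of them, "The progression of lacunar infarcts and microbleeds will be evaluated as the appearance of at least one new lesion, respectively". The third is white matter hyperintensity progression on a visual scale from 0 to 9. Microbleeds are stressed, but no testing order or split of alpha is given.

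Table 1 lists the circulating markers. "Plasminogen activator inhibitor-1 (PAI-1) antigen" is printed twice there, with a change of capitals, in the coagulation block.

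**The concern.** Two things are at stake, both modest.

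- **Power.** The cohort is 194 patients (section 3) and its size was set by feasibility (section 2.2), so power cannot be bought with more patients. Bonferroni compares every marker with the same threshold, even after others have been rejected. Holm relaxes the threshold at each rejection without weakening the guarantee, so the plain version gives away a little power for nothing.
- **Error across outcomes.** The correction is tied to models, and the primary endpoint needs at least three of them. If each is corrected on its own, the stated aim of countering multiple comparisons is met inside each model but not over the endpoint as a whole. Section 2.8 intends the results to inform the design and sizing of later studies, so a false lead would carry forward.

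**Working it through.** The article states no adjusted threshold, power or error rate, so there is no figure of its own to reproduce. A two-sided alpha of 0.05 is assumed throughout.

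**1. Count of markers (Table 1).** Endothelial 2, inflammatory 12, metalloproteinases and inhibitors 8, coagulation 7 as printed or 6 with PAI-1 counted once: 2 + 12 + 8 + 6 = 28. Adding the ten polymorphisms gives 38. The miRNA profile has no stated size and is left out.

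**2. Thresholds over the 28 markers.**
- Bonferroni: 0.05/28 = 0.0018 for every marker (|z| > 3.124).
- Holm: 0.05/28 = 0.00179 for the smallest p-value, 0.05/27 = 0.00185 for the next, and 0.05/19 = 0.00263 for the tenth once nine are rejected. No step is stricter than Bonferroni, so Holm rejects everything that Bonferroni rejects. Its family-wise error is also held at 0.05, whatever the correlation.

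**3. Size of the Holm gain.** This was simulated with 28 z-statistics in blocks of 2, 12, 8 and 6, correlations of 0.3 to 0.7 within blocks and 0.1 to 0.2 between them, and noncentrality 2.8 to 3.5 for each real marker. These values are assumptions. With one real marker the gain is essentially zero. With ten it reaches about 2.5 points. Bonferroni power per marker at noncentrality 2.8 is 37%. In a larger assumed family of 3 × 38 = 114 tests with three real effects at noncentrality 3.5, the gain is only about 0.2 points.

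**4. Error across the three primary components, if corrected per model.**
- Each component held at exactly 0.05, independent: 1 − 0.95³ = 0.143.
- The 28 tests in each also independent: 1 − (1 − 0.05/28)^84 = 0.139.
- Any dependence: at most 3 × 0.05 = 0.15.
- With 38 markers tested one at a time and correlated across the whole panel, the figure falls to 9.5% at correlation 0.5 and 6.1% at 0.7.
- If the divisor already covers all outcome models, the error is at most 5% and this part falls away.

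**5. Does marker correlation make Bonferroni wasteful?** It depends on the type of model.
- One marker at a time: true error over 28 tests is 4.7%, 4.2% and 3.3–3.4% at within-block correlation 0.3, 0.5 and 0.7. A max-T correction raises power at noncentrality 2.8 from 37% to between 38% and 43%.
- All markers mutually adjusted: the correlation of the test statistics follows the inverse of the marker correlation matrix and is close to zero. Bonferroni error is 4.7–4.9%, and max-T gains under 1 point.

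**The case against.** The strongest case against the point is that Bonferroni is valid, that the article claims only preliminary evidence (section 4), and that a condensed article commonly leaves the family of tests to a fuller document. All of that stands, so the missing family definition is not held against the plan. What remains is a method that the text does fix, and one that can be improved at no cost in error control.

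Three stronger readings are tempting, and the documents do not support them.

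- **That Bonferroni is too strict for these correlated panels.** This fits one-marker-at-a-time tests. Section 2.8 speaks of independent effects of all relevant markers, which suggests mutual adjustment, where Bonferroni is nearly exact. One-at-a-time models with clinical covariates cannot be ruled out, but even there the max-T gain is about 1 to 5 points. Simple permutation of the outcome does not preserve covariate effects in an adjusted model, so max-T would need an adapted scheme.
- **That the chance of a false claim is 37%.** That is 1 − 0.95⁹. It needs a per-model correction, nine outcome models (the six SVD features of section 2.4 plus three progression measures), independence between features measured in the same patients, and exactly 5% error in each. The primary endpoint has three components, and the article does not state that the correction is per model.
- **That one wider family would give the same protection with more power.** Moving from per-model Bonferroni to one family of 114 tests gives more protection and less power: about 61% falls to 49–52% in the block simulations. Restricting claims to microbleeds avoids that loss for microbleeds only by giving up significance claims on the other outcomes.

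**Conclusion.** The point holds as a minor improvement. Holm over the same tests dominates plain Bonferroni, with a gain of zero to about 2.5 points for 28 markers; the size rests on assumed effects and on how many markers are real. The excess error across the primary components, up to about 14% if they are independent, is conditional on a per-model correction, which is the natural reading of section 2.8 but is not stated there. A lead outcome removes that excess under either reading. The repeated PAI-1 entry matters only if someone takes the divisor from the printed list. Nothing here makes the planned analysis invalid.

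**What to change.** In section 2.8:

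- Replace Bonferroni with Holm and apply it to the marker terms, not to the clinical covariates. Count PAI-1 once.
- Say whether the ten polymorphisms and the miRNA profile belong to the family. With the polymorphisms the first Holm step moves from 0.05/28 = 0.0018 to 0.05/38 = 0.0013, so the choice matters more than the change of procedure.
- Take new microbleeds, which the plan already stresses, as the lead outcome. Report the other outcome models as exploratory, with intervals and no significance claim.
- Treat permutation max-T as optional. It is worth considering only if markers are tested one at a time, and with a scheme that preserves covariate effects.

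The cost is a sentence or two of text and no loss of error control. The real downside is that fewer outcomes carry a significance claim: lacunar infarct and white matter progression would be reported descriptively.
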